### Study design and setting

A cluster-randomised, controlled, multicentre, prospective longitudinal study with a waitlist control group design was conducted to test the above research hypotheses.

All day-care centres participating in the study (cluster) were randomly assigned to the intervention or control group at baseline (random selection). The cluster was stratified by region (the Northeast, the Southeast, and the West). In order to guarantee that the sequence would be concealed until the intervention and control groups were assigned, all day-care centre staff were trained on the study protocol, instruments, and screening before the randomisation. The informed consent of the day-care users and their caregivers were also collected before the randomisation (see Fig. 1). Day-care centres were informed of their group allocation in written form by the study headquarters. During the 6-month intervention phase, the day-care centres in the intervention group carry out the MAKS treatment after their staff receive training. The caregivers receive a brief telephone intervention by counsellors with training in psychotherapy. The day-care centres in the control group do not carry out any additional project-specific treatment but continue providing “care as usual”. This is the accepted standard of care in day-care centres. Because we are investigating a non-pharmacological intervention, neither the staff carrying out the MAKS therapy nor the people with cognitive impairment are blinded. Six months after baseline, the day-care centres’ staff in the control group will also undergo training in MAKS therapy. At the end of the 6-month intervention phase, the day-care centres in both the intervention and control groups will freely decide whether or not to continue the MAKS treatment or to introduce the treatment, respectively, including the level of intensity. The observation period is 2 years with a total of four measurement points (baseline and after 6, 12, and 24 months). Data are collected by means of psychometric tests, the day-care centres’ documentation, and computer-assisted telephone interviews (CATIs) with the caregivers. All procedures were approved by the Friedrich Alexander University Erlangen-Nuremberg Ethics Committee. The external GKV Spitzenverband was closely informed of the progress of the study and achieved milestones as determined in the trial application. The study design is presented in Fig. 1. In the case of important protocol modifications, we will inform the Ethics Committee, the funders, the day-care centres, and the platform for the trial registry. Trial registration data are presented in Table 1.

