### Analysis

#### Data analysis

Only researchers at the study centre in collaboration with the Institute of Health Economics and Health Care Management will assess the results. Our cooperation partner will check the plausibility of the data independently. Thus, there is no need for a data monitoring committee.

The data analyses will be performed with the aid of the “IBM SPSS Statistics 21” software.

If at least 80% of the items on a test have been answered, we will impute missing values from the mean score of the existing items. However, if more than 20% of the items on a test are missing for any given person (e.g. because a participant refuses to complete the test), we will compute the score according to the expectation maximum (EM) algorithm, which uses the variables that explain the greatest proportion of variance in the missing variable.

All changes to the data due to checking for errors, data quality management, or the handling of missing values will be documented.

In order to be able to assess the quality of the randomisation, the baseline data from the intervention and control groups will be examined for statistically significant differences.

The two hypotheses on the efficacy of the interventions in people with cognitive impairment and their caregivers will be tested by computing multiple regression analyses. The transition to institutionalised care as an event will be represented by a Kaplan-Meier curve for the intervention and control groups. The hypothesis on the transition to institutionalised care will be evaluated by Cox regression analysis.

As the primary outcome variables cannot be tested at follow-up in participants who dropped out of the study, the primary data analysis strategy will be “as treated”. The level of statistical significance will be set at *p* = 0.05. Results with an alpha error of less than 10% will be classified as statistical trends.

Subgroups will also be analysed exploratively, sub-divided in accordance with the severity of cognitive impairment and the mean frequency of attendance at the day-care centre per week.

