### Strengths and limitations of the study design

Strengths of the study design are the cluster randomisation, the long follow-up period of 2 years, the use of a manualised treatment that has already been evaluated in nursing homes [15, 16, 22], the naturalistic setting in care institutions which are already part of the German health care system, and the focus on the dyad consisting of both the person with cognitive impairment and his/her informal caregiver.

Moreover, due to the recruitment of day-care centres throughout Germany and the balanced ratio of urban to rural day-care centres run by a wide variety of organisations (local authorities, non-profit, and private), the external validity of the study is high. The naturalistic design – in which the study has no influence on the number of days the people with cognitive impairment attend the day-care centres (days of treatment in the intervention group) – also makes it possible to analyse subgroups in order to determine the necessary intensity of the treatment.

We decided on cluster randomisation rather than randomisation on the participant level for two reasons. If two groups that are separate in terms of rooms and staff – one treatment group and one control group – were to take place at the same day-care centre, only a very few very large day-care centres would have the necessary capacity. These day-care centres are not representative of the general healthcare situation and would thus markedly reduce the external validity. In addition, implementing two study groups simultaneously in the same institution would be associated with a risk of halo effects by which the treatment might influence the control group.

The possible disadvantage of a systematic difference between the arms of the study arising by chance from the cluster randomisation is offset both by the large number of 34 randomised day-care centres and by the stratification by region [51].

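### Baseline significance tests cannot assess how well 34 centres were randomised; describe baseline data instead, and state baseline and region adjustment in a model that accounts for centre

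*Protocol article*

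**What the plan says.** The Data analysis section gives both a method and a purpose. To judge how well the allocation worked, "the baseline data from the intervention and control groups will be examined for statistically significant differences". Shortly afterwards it sets the general threshold: "The level of statistical significance will be set at *p* = 0.05". It adds a second band: "Results with an alpha error of less than 10% will be classified as statistical trends". It names neither the test nor the unit, user or centre, for the baseline comparison.

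On the design, the section Study design and setting says: "All day-care centres participating in the study (cluster) were randomly assigned to the intervention or control group at baseline". Allocation was stratified by three regions, and consent of users and caregivers was collected beforehand. The efficacy hypotheses are to be tested by multiple regression, with no covariates listed.

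Under Strengths and limitations of the study design, the article accepts that the arms may differ systematically by chance. It says that this disadvantage "is offset both by the large number of 34 randomised day-care centres" and by the regional stratification.

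**The concern.** A baseline significance test asks whether a difference is larger than chance allocation would produce. If the centres were properly randomised, the answer is known in advance, because every such null hypothesis is true by design. The p-value then says nothing about how well the randomisation was done. It also does not say whether an imbalance matters. That depends on the size of the difference and on how strongly the variable predicts the outcome.

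Two misleading statements could follow. Chance differences may be reported as a defect of the randomisation, or an absence of significant differences may be reported as proof of balance. Because centres were randomised, there is a further problem: tests that treat users of the same centre as independent reject too often. The article mentions no allowance for clustering in any analysis.

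**Working it through.** The article states no figure for the baseline tests, so there is none to reproduce.

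**Inputs from the article**
- Level 0.05 (Data analysis). Sidedness is not stated; two-sided is used here.
- 34 centres, and 453 dyads included (Caregivers, under Eligibility of participants): m = 453/34 = 13.3 users per centre.
- Four visited centres are 24% of the intervention group (Data quality management): 4/0.24 = 16.7, so about 17 centres per arm.
- Planned size 346 (Sample size estimation): m = 346/34 = 10.2, used as a sensitivity value.

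**Assumed, not in the article**
- 20 baseline variables. The Measures section names four primary and five secondary outcome scores plus a list of history items, so this is plausible.
- Intracluster correlation (ICC) of 0.02 to 0.10.

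**Step 1: multiplicity alone.** With k independent tests at a true 5% level, P(at least one significant) = 1 − 0.95^k.
- k = 10: 40%
- k = 20: 64%, with 20 × 0.05 = 1 expected false alarm

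Correlation between variables changes the probability but not the expected count.

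**Step 2: user-level tests that ignore centre.** Design effect DE = 1 + (m − 1) × ICC; true rejection rate = 2 × [1 − Φ(1.96/√DE)].

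| ICC | DE (m = 13.3) | Rejection rate | Expected in 20 tests | Rejection rate (m = 10.2) |
|---|---|---|---|---|
| 0.02 | 1.25 | 7.9% | 1.6 | 7.2% |
| 0.05 | 1.62 | 12.3% | 2.5 | 10.5% |
| 0.10 | 2.23 | 19.0% | 3.8 | 15.7% |

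A simulation with 17 centres per arm and 453 users gave 7.8%, 12.0% and 19.4%. Tests on centre means stayed at 4.8% to 5.3%.

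**Step 3: what a non-significant result can hide.** With 453 users split about equally, a user-level test is non-significant below about 1.96 × 2/√453 = 0.184 SD. At an assumed baseline–outcome correlation of 0.6 to 0.8, such a difference shifts an unadjusted outcome comparison by 0.184 × 0.6 = 0.11 to 0.184 × 0.8 = 0.15 SD. If the planned f² = 0.06 is read as a two-group effect, d = 2√0.06 = 0.49, and the shift is about 23% to 30% of it. This matters only in an unadjusted analysis.

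**Step 4: checking the alternative by simulation** (assumed baseline–outcome correlation 0.5 or 0.7, ICC 0 to 0.10, region not simulated).
- Centre-level analysis with the baseline score always included: type I error 4.5% to 5.3%. The standard error falls by about 12% (correlation 0.5) or 27% (correlation 0.7).
- Centre-level analysis adjusted only when the baseline test was significant: type I error 2.6% to 4.8%. This is conservative, so the loss is precision.
- User-level regression with the baseline score but no centre term: type I error 12% to 14% at ICC 0.05 and 19% at ICC 0.10.

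**The case against.** The strongest reply is that the sentence prescribes a descriptive check that changes no primary result. Nothing ties it to the efficacy model, and every magnitude above rests on assumed values. Much of this stands.

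- **Adjustment.** A reader might infer that the primary analyses will be unadjusted, or that the tests will choose the covariates. The article says neither. A condensed article may leave covariates to the full plan, and there are hints of adjustment: the regression is called multiple, the first hypothesis concerns change over time, and the cost model adjusts for baseline costs. The planned 270 is also reproduced by an omnibus F test with nine predictors (an assumed count), whereas a single group coefficient would need 133.
- **Unit of the tests.** A reader might take user-level testing as stated. It is not. The excess rejection in Step 2 is conditional on it, while the multiplicity in Step 1 is not.
- **Use as an audit.** Baseline tests can hint at selective recruitment or subverted allocation. Consent before allocation leaves little room for the former. The text does not settle whether all baseline measurements preceded disclosure of the allocation, so a significant difference is mostly, not necessarily wholly, chance.

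What does not fall is the stated purpose. The article gives these tests the task of assessing randomisation quality, and they cannot do it.

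**Conclusion.** The point holds in a limited form. The planned tests do not measure the quality of the randomisation. Under proper allocation they produce at least one false alarm with probability 64% in 20 independent tests at a true 5% level. The rate per test is about 7.9%, 12% or 19% only if users are tested without regard to centre, at the assumed ICCs. The appeal to "the large number of 34 randomised day-care centres" and region strata does not rescue the check: these limit chance imbalance but do not ensure balance on baseline ETAM, MMSE, BSFC-s or WHO-5.

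The documents do not support a claim that the randomisation was faulty, that the primary result is biased, or that adjustment was rejected. The harm is a misleading report on the randomisation and, if adjustment were made to depend on the tests, lost precision.

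**What to change.** - Delete the baseline significance tests.
- Report baseline data descriptively by arm, for users and for centres, for example with standardised differences.
- Judge randomisation quality from an account of how the sequence was generated and concealed.
- State that each primary regression includes the baseline value of its outcome and the region stratum, whatever the baseline table shows, in a model that accounts for centre (for example a random centre effect or a centre-level analysis). Baseline and region alone are not enough, because a user-level regression without a centre term would keep the inflated type I error shown in Step 4.

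Adjustment deals with chance imbalance and precision. It does not assess the randomisation, so the second and third items are needed as well. The cost is a few sentences and a simpler baseline table, using data already planned.

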**Methods/design:**

The present study therefore investigates the effectiveness of a combination of a multicomponent activation therapy for people with mild cognitive impairment (MCI) or mild to moderate dementia at day-care centres and a brief telephone intervention for their informal caregivers. The study is conducted as a cluster-randomised intervention trial at 34 day-care centres in Germany with a 6-month treatment phase. The centres in the waitlist control group provide “care as usual”. A power analysis indicated that 346 people should initially be included in the study. The primary endpoints of the study include the ability to perform activities of daily living (ADL) and cognitive capacities on the side of the day-care centre users and the subjectively perceived burden and well-being of the informal caregivers. The total duration of the study is 3 years, during which data are collected both by the psychometric testing of the people with cognitive impairment and by telephone interviews with informal caregivers.

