### Sample size estimation

A power analysis was computed on the basis of the authors’ previous experience with the MAKS study in nursing homes [15, 16, 22]. In contrast to the procedure in the MAKS study in nursing homes, the intervention in the DeTaMAKS project had a lower treatment intensity and a shorter duration, and therefore the effect was expected to be markedly lower. We conservatively set an expected effect size of f^2^ = 0.06 for the primary outcome and alpha error of 0.05 and a statistical power of 0.80 and obtained a total sample size of approximately 270 people attending a day-care centre for at least 6 months. Based on pilot study we assumed fluctuation in day-care centre users of 22% over 6 months. Therefore, we concluded that a total of 346 people should initially be included in the study.

The results of the MAKS study in nursing homes also showed that 69% of eligible candidates were willing to take part in the study. The pilot study showed that 56% of the day-care centre users who were screened fulfilled the required criteria for inclusion. This means that a total pool of 1086 day-care centre users was needed to achieve the required sample size. If we assumed approximately 33 users per week, we needed to recruit at least 32 day-care centres.

These day-care centres were large enough to have the space and staff required to carry out the project in accordance with the prescribed conditions.

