### Data quality management

All of the groups involved in the study (MAKS therapists, counsellors for the informal caregivers, testers, CATI interviewers, and monitors at the day-care centres) are thoroughly trained for their respective tasks by the study headquarters staff. When they have questions, the members of all groups could contact the study headquarters at any time by phone or in writing.

In order to ensure the validity of the data, the data sources (tests, CATIs, day-care centres) are subjected to a random internal audit. To obtain evidence of the inter-rater reliability of the ETAM test and the CATIs, 5% of the baseline data were collected with the participation of a second person who is there to observe. Four (24%) of the day-care centres in the intervention group will be visited by personnel from the study headquarters during the first 6 months to monitor how the MAKS therapy is conducted (treatment adherence), the quality of the documentation (deviations from the manual and extraordinary events), and the attendance of the study participants.

The quality of the data is guaranteed by strict data monitoring at the study headquarters over the entire period of data collection. In addition, as some of the data are collected in two ways (e.g. care level) at the day-care centre and via a CATI with the caregiver, independent source document verification will be performed. Plausibility checks and logical considerations about the relationships between associated variables will be performed. Regular backups will be carried out and saved on an external hard drive.

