#### Economic evaluation/ analysis

The valuation of resource use will be based on the valuation rates by Bock et al. [49]. The costs of the intervention include the training time and supervision of day-care centre staff, and materials (manuals, handbooks, etc.)., To analyse cost difference between groups, a multivariable model with a gamma distribution will be used to account for the skewed distribution of the data [50], adjusted for baseline costs. A 95-% confidence interval for the adjusted cost difference will be estimated from 1000 bootstrap replications. A cost-utility analysis from a societal perspective will be performed in which the quality of life of both day-care users and informal caregivers will be assessed. To calculate the quality-adjusted life years for day-care users regarding the time remaining at home, the quality of life values will be set to 0 from the day of admission to a nursing home or death. Moreover, a budget impact analysis will be computed to address changes in the expenses of the health care system if the MAKS therapy shows significant effects.

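### Centres are randomised, but the primary regression and the sample size make no allowance for centre, so the 5% error rate fails if outcomes within a centre are correlated.

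*Protocol article*

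**What the plan says.** The design is clear about the unit of allocation. Study design and setting: "All day-care centres participating in the study (cluster) were randomly assigned to the intervention or control group at baseline". On stratification, the same section says "The cluster was stratified by region (the Northeast, the Southeast, and the West"). The abstract gives the number of clusters: "The study is conducted as a cluster-randomised intervention trial at 34 day-care centres in Germany with a 6-month treatment phase".

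The Data analysis section says that the two efficacy hypotheses, one for users and one for caregivers, "will be tested by computing multiple regression analyses". On the error rate it says "The level of statistical significance will be set at" p = 0.05. The move to institutional care is tested by Cox regression. In the economic evaluation, the confidence interval for the cost difference "will be estimated from 1000 bootstrap replications".

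Sample size estimation starts from an "expected effect size of f^2^ = 0.06 for the primary outcome", alpha 0.05 and power 0.80. It arrives at about 270 people, and inflates this for 22% turnover to 346.

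The article nowhere mentions an intracluster correlation, a design effect, a random centre effect, generalised estimating equations, cluster-robust standard errors or an analysis of centre means.

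**The concern.** Users of one centre share staff, group sessions, local services and possibly the person who tests them. Two users of the same centre are then likely to be more alike than two users of different centres. Arm varies only between centres, so this shared variation goes straight into the treatment comparison. A regression that counts each person as an independent unit leaves it out of the standard error.

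At stake are the tests on the four primary outcomes: ETAM and MMSE for users, BSFC-s and WHO-5 for caregivers. A significant result could reflect ordinary differences between centres more often than the nominal 5% allows. The power statement has the same gap, because 270 correlated people carry less information than 270 independent ones.

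**Working it through.** **The plan's own figures.** Inputs from Sample size estimation: f² = 0.06, alpha 0.05, power 0.80, 22% turnover. The number of predictors is not stated. An overall F test in multiple regression with independent people (noncentrality f² × N) needs N = 259 with 8 predictors, 270 with 9 and 280 with 10. So 270 is reproduced if nine predictors are assumed. Then 270/0.78 = 346.2, the stated 346. No clustering term is needed at either step. A test of the treatment term alone (1 degree of freedom) would need 133, so the reproduction depends on the nine-predictor assumption.

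**Clusters.** There are 34 centres. Data quality management says "Four (24%) of the day-care centres in the intervention group will be visited by personnel from the study headquarters", and 4/0.24 is about 17, so the split is about 17 to 17.

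**Analysed people per centre (m).**
- Recruited sample: 453 dyads (Eligibility of participants, Caregivers), less 22%: 453 × 0.78 = 353; 353/34 = 10.4.
- Planned sample: 270/34 = 7.9.

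**Formulas.** Design effect DE = 1 + (m − 1) × ICC. The unadjusted standard error is 1/√DE of the true one. The true two-sided error of a nominal 5% test is 2 × [1 − Φ(1.96/√DE)]. The effective sample size is N/DE. The ICC is an assumption, shown as a range; the relevant one is what remains after covariate adjustment.

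| Assumed ICC | m | DE | SE ratio | True error | Effective N |
|---|---|---|---|---|---|
| 0.01 | 10.4 | 1.09 | 0.96 | 6.1% | 323 of 353 |
| 0.05 | 10.4 | 1.47 | 0.82 | 10.6% | 240 of 353 |
| 0.10 | 10.4 | 1.94 | 0.72 | 15.9% | 182 of 353 |
| 0.01 | 7.9 | 1.07 | 0.97 | 5.8% | 252 of 270 |
| 0.05 | 7.9 | 1.35 | 0.86 | 9.1% | 200 of 270 |
| 0.10 | 7.9 | 1.69 | 0.77 | 13.2% | 159 of 270 |

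**Simulation check.** With 10,000 runs per setting, 17 against 17 centres and 270 people in equal-sized centres, the unadjusted analysis rejected a true null in 8.9% of runs at ICC 0.05 and 13.0% at ICC 0.10. With unequal centre sizes (coefficient of variation 0.4) the figures were 10.2% and 14.2%. A t test on centre means with 32 degrees of freedom stayed between 4.5% and 5.4% in every setting.

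**Does recruiting more people help?** For power, up to a point. The 353 people expected are worth at least 270 independent ones while DE is at most 353/270 = 1.31, that is ICC up to 0.31/9.4 = 0.03. The error rate gets worse, because it rises with m.

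**The case against.** The strongest reply is that the article names a technique and gives no full specification. It lists no model terms at all, not even arm or baseline score, so the absence of a centre term could be condensation, and a statistical analysis plan that is not shown could add one. This stands as a caution, but it does not remove the point. The article fixes the method for the confirmatory tests, and the method it names does not match the randomised unit. It also gives finer detail elsewhere: a threshold for imputing items, the gamma distribution, the number of bootstrap replications. Its one remark on a statistical drawback of cluster randomisation, under Strengths and limitations of the study design, concerns chance imbalance between arms, not correlation within centres.

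One could also argue that 270 hides an allowance for clustering, since a 1-degree-of-freedom test needs only 133 and 270/133 is about 2.0. The section presents 270 as following from effect size, alpha and power alone, so the text gives no support for this.

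Four stronger readings are tempting and should not be drawn.
- That every primary p-value is wrong. The inflation depends on an ICC that the article does not give, and at 0.01 it is slight.
- That caregiver outcomes are affected to the same degree. Caregivers are counselled one to one by telephone by two counsellors and rate themselves by telephone interview. Some correlation through shared day-care and region is possible, but there is less reason to expect it. The 22% loss is also a figure for users, so m = 10.4 does not carry over exactly.
- That the Cox result and the cost interval are too narrow. The Cox variance estimator and the bootstrap resampling unit are simply not stated, and an article may leave them to a fuller document.
- That leaving region out of the model makes standard errors too small. Omitting a stratification factor tends to make them too large.

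**Conclusion.** The point holds for the primary regression and for the sample size, conditional on a positive ICC. Followed as written, the analysis has a true error of about 6% to 16% for ICCs of 0.01 to 0.10 with about 10 analysed users per centre, and about 6% to 13% at the planned 270. These figures assume near-equal centre sizes; the simulation with unequal sizes gave somewhat higher error at ICCs of 0.05 and 0.10. The case is strongest for ETAM and MMSE, and applies in weaker form to BSFC-s and WHO-5. The stated 80% power for 270 people is an ICC-of-zero figure. The document neither claims nor supports an ICC near zero, which the named method would need to be valid. For the Cox model and the bootstrap there is something to specify, but no demonstrated error. This should be settled before the primary results are analysed.

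**What to change.** For each primary outcome, replace multiple regression by a linear mixed model with a random intercept for centre, fixed effects for arm, region and baseline score, and small-sample degrees of freedom suited to 34 clusters. An analysis of centre-level summaries is an acceptable alternative. Region and baseline score are there for precision and consistency with the design; the centre term is what corrects the error rate. Report the ICC for each primary outcome.

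In Sample size estimation, state that 80% power for 270 people assumes an ICC of zero, or restate it over a range. With 34 centres, information equal to 270 independent people needs N = 270 × (1 − ICC)/(1 − 270 × ICC/34): about 291, 426 and 1181 analysed people at ICCs of 0.01, 0.05 and 0.10.

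For consistency, specify centre-robust variance or a shared frailty in the Cox model, and name the centre as the bootstrap resampling unit. If centres are resampled within arm and region, there are only about 34/6 = 5.7 per cell, and an uncorrected bootstrap would understate the standard error by a factor of about √(4.7/5.7) = 0.91, so a correction for few centres is needed.

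The change is to wording and analysis code, with no new data. The price is wider intervals and lower stated power.
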